### Outcomes

**
*Primary and secondary*
**

The primary outcome is SHS exposure at homes at 10 months and 16 months as assessed by the change in mean urine cotinine levels among women and or children of the smoker at the individual level. The secondary outcomes will include individual level self-reports of smoking within homes, particulate matter 2.5, harm reduction (reduction in the number of cigarettes smoked), quitting of smoking, blood pressure, Fagenstrom Nicotine dependence score, and comorbidities. Individual level assessment of Fev1/Fev6 will also be carried out with handheld spirometry considering a cut off of 73% to be indicative of COPD which is also a secondary outcome. Forced expiratory volume in 1 second (FEV1) is the maximum amount of air that the subject can forcibly expel during the first second following maximal inhalation.
^
46
^ Similarly, forced expiratory volume in 6 seconds (FEV6) is the volume of forcibly exhaled air measured during 6 seconds
^
47
^ which can be measured by handheld spirometry.

Cluster level assessment of 2.5 particulate matter in homes will also be done with air quality monitors. Monitoring and assessing intervention in terms of development of a training booklet, educational material, number of meetings organized, proportion of self-help group members in the area participating and inviting local self-government members to participate.

In order to understand the reasons for success and failure, in-depth interviews of men who have successfully quit smoking within homes, quit smoking completely, ASHAs, and health workers will be conducted. Focus group discussions of wives of smokers who quit smoking within homes and those who reduced the number of cigarettes will be conducted.

*Data analysis and statistical plan*: Data will be entered electronically on a secure file storage system and password protected. Data will be anonymised by assigning a unique identification number to each smoker. Outcome data will be reported in accordance with the Standard Protocol Items: Recommendation for Intervention Trials (SPIRIT). All the smokers will be included in the analysis regardless of reduction in smoking within homes.

**
*Participant flow*
**

30 clusters will be randomly assigned into two groups and will receive intended intervention and will be analyzed for primary outcome of urinary cotinine. For each group losses and exclusion of clusters and individual participants will be recorded (
Figure 1).

*Baseline data*: The baseline data will be presented for both clusters and individuals as the risk of chance imbalances are greater with clusters.

*Numbers analyzed*: We plan to analyze 30 clusters with at least 300 indoor smokers in each arm. The urine cotinine of the women and children will be obtained from 300 women and or children in each arm. The indoor home values of 2.5 PM will be obtained from 300 households in each arm. Similarly, the lung function values as indicated by FeV1/FeV6 will be assessed among 300 each in the intervention and control group.

*Outcomes and estimation*: The difference in mean cotinine levels among the clusters in the intervention and control group with 95% CI will be estimated. The intracluster correlation coefficient for each outcome will be reported. Adjusted estimates of clustering will also be provided. Cox’s proportional hazards will be calculated for quitting, harm reduction, blood pressure values. This is to determine the effectiveness of an intervention based on partnering with women’s SHG’s to reduce indoor tobacco smoking by measuring urinary cotinine levels.

A repeated-measures ANOVA will be used to compare the mean urinary cotinine concentration between groups, before and after intervention.

Analysis for self-reported quit rates will be assessed by a Cox proportional hazards model. Generalised linear mixed effect models will be used to test between cluster differences from baseline to each follow up period for each outcome indicator.

We will use an intention to treat approach in analysis. A multilevel model will be used for analysis using the generalized linear mixed effect model which will also adjust for individual covariates. Key variables will be measured at baseline and then compared between arms to check balance; and if both arms are unbalanced with respect to any relevant factors, which can happen given that the unit of randomization is the cluster instead of the individual, those factors will be adjusted for in the final analysis so as to address potential confounding. Analysis for SHS exposure rates and quit rates will be assessed by a Cox proportional hazards model.
•To correlate the urinary cotinine levels with the second-hand smoke in the home environment: correlation and linear regression analysis will be carried out by Pearson’s correlation if it follows a normal distribution and Spearman if it is a non-normal distribution.The difference in cotinine levels will be analysed by comparing the urine level of cotinine at the end of follow up, adjusted for the baseline value, by using linear mixed model or GEE to allow for cluster effect.•To measure the effectiveness of the intervention among smokers by measuring their FeV1/FeV6 using COPD6.To determine the effectiveness of the intervention in improvement of lung function the ratio of FeV1/FeV6 will be measured pre- and post-intervention and the mean difference between the groups will be assessed by a paired t-test.
**
*Qualitative data analysis*
**
Interview guides will be developed for in-depth interviews, key-informant interviews and focus group discussions by extensive formative research with literature reviews and taking expert opinions. A list of pre-determined open-ended questions will be used in the interview guides. Probing questions will be asked to explore the topic in-depth. An informed verbal consent will be obtained for participating in the interview and for audio recording the session. The interviews will then be conducted in the regional language, Malayalam. The audio recorded data will be then transcribed verbatim and translated to English. The typed transcripts will then be reviewed for accuracy, completion and familiarization and then manually coded to identify the emerging themes and subthemes. Semi-structured interviews and focus groups will be audio-recorded, transcribed verbatim and anonymised before being coded. Conclusions will then be arrived at by data triangulation.Data will be analysed inductively using the grounded theory. Appropriate codes and sub-codes will be generated. Data will be analysed thematically to elicit appropriate themes and sub-themes. Interviews in local languages will be transcribed and the analysis will be conducted by researchers fluent in these languages.To understand the impact of the intervention among smokers who quit, those who showed reduced smoking, those who did not stop smoking within homes, and households where the smokers stopped smoking within homes, focus group discussions will be conducted with spouses of the smokers. These focus group discussions will enable the participants to share their experience. Focus group discussions will comprise of 6-8 wives of smokers who quit smoking within homes and or those who reduced the number of cigarrettes/bidis. The other focus groups will be with those who have quit or reduced the number of cigarettes smoked and among those who have not, in order to identify barriers to smoking cessation within homes. The focus groups will also seek to identify factors that affected participation in the meetings, motivation due to the educational sessions, and the factors that most helped to quit smoking within homes or cessation or harm reduction.The fidelity of the intervention will be assessed by the number of meetings conducted in an area, the number of smoking persons and household members attending, and the number of influencers of smokers contacted. At the end of the study focus group discussions will be conducted among 6-8 quitters, those who have reduced the number of cigarettes/bidis smoked and those who did not make any change at all. Apart from the focus group discussions, in-depth interviews will be conducted with the self-help group volunteers. These interviews will be conducted at the end of the intervention among about self-help group volunteers who were part of the intervention, councillors, urban primary health centre MO, and a junior public health nurse to identify the key elements that might have helped in effective implementation and good outcomes.
*Ethical issues*: Any adverse events will be recorded and reported to the Chair of the Trial Steering Committee and the Chair of the Ethics Committee. Institutional Ethical Committee approval has been obtained vide letter dated 18-10-2022 from Amrita Institute of Medical Sciences (IEC-AIMS-2022-COMM-284). The protocol V2 was submitted and approved by ethical committee vide above. Informed consent and assent will be obtained from the respective participants by the coordinator of the study. The investigators will only have access to the data.
*Dissemination*: A dissemination will be carried out in Kochi with the participation of all stakeholders. The results of the study will be disseminated to all the stakeholders including the community, state and district NCD control officers. Following this the results will also be disseminated through publication.
*Public involvement*: The local self-government has been taken into confidence and they are fully supportive of this venture. Local steering committees have been formed in the intervention clusters to guide and support the intervention.

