**Smoker**				
Smoking within homes (self-reports)		✓	✓	✓
Fagenstrom nicotine dependence score		✓	✓	✓
No of cigarettes smoked daily		✓	✓	✓
No of persons who have quit			✓	✓
Blood Pressure		✓	✓	✓
BMI		✓	✓	✓
Fev1/Fev6		✓	✓	✓
*Air pollution	PM 2.5	✓	✓	✓
	PM 10	✓	✓	✓
	CO _2_	✓	✓	✓
Women	Cotinine	✓	✓	✓
Child	Cotinine	✓	✓	✓
BMI	Child	✓	✓	✓
Resp. Infection	Child	✓	✓	✓
	Woman	✓	✓	✓
Process evaluation	In depth interview			✓
	FGD			✓

A door-to-door initial survey will be conducted following a training to the data collectors. After ascertaining the households where the male member smokes the interviews of the smoker, wife/close female relative, and child will be conducted. The interviews will be conducted separately for the husband and wife/close relative who is a woman. After the interview, Fev1/FeV6 ratio among the smokers will be assessed with the Vitalograph COPD-6 screener device. The women and child of the household will be asked to keep the urine sample in a sample bottle provided which is then placed in an auto seal pouch. These samples will be collected from all the houses and transported to the laboratory by maintaining cold chain at a temperature between 2-8 degrees C. The urinary cotinine levels among the women and children of the smoking households will be assessed in this urine sample. The cotinine levels will be assessed among the spouse of the smoker or among a woman who stays at home for a longer duration and a child up to 18 years of age. If there is more than one child in the house, the youngest child older than 1 year will be chosen. All houses may not have children; therefore, it is necessary to take both women and children’s cotinine levels. This would also be an important advocacy tool as the children’s cotinine levels can be used to influence the smoker. The urine cotinine level will be measured at 6, 10, and 16 months with the help of Cal biotech’s ELISA kit which will measure cotinine levels by ELISA (solid phase competitive ELISA). The test was calibrated and standardised in a pilot study among households of smokers and non-smokers and differences ascertained.

Quality of data collected will be ensured by training and retraining of the data collectors. The data collection forms are provided.
^
40
^
^,^
^
41
^ The laboratory tests will be carried out after validation. Data entry will be done with back up and range check-ups will be done for data values.

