### Sample size calculation

Based on previous studies we assume an ICC of 0.06.
^
43
^ To detect a minimal difference of 0.03ng/ml in cotinine levels between groups,
^
44
^ at 80% power with a two-sided alfa of 0.05, the estimated sample size was 113 indoor smokers per arm for individual randomization. Since one of the studies in the slum area of Ernakulam had found a prevalence of indoor smoking of 16% and considering slums above 100 households it is assumed that the expected number of smokers within household will be 20 per cluster with variability in clusters. Hence we estimated the sample size for unequal cluster size,
^
45
^ with a CV of 0.45 and VIF=2.4. The estimated sample size was 271 and 14 clusters per arm. Further we assumed a drop-out rate of 10%, the final sample size was rounded to 300 per arm and 15 clusters.

**
*Randomisation*
**

The trial has been registered in Clinical Trials Registry – India
CTRI/2021/06/034478.

A simple randomisation will be undertaken of the selected slums in the urban and peri-urban areas to receive intervention or not by a computer-generated random number list.

Allocation concealment: Allocation will be based on clusters and the allocation will be done after the baseline survey assessment by a statistician not directly related to the study. There is no allocation concealment. All the indoor smokers will be recruited and they will be selected before randomising clusters.

*Implementation*: Meetings will be conducted with the Kochi Corporation and District Medical Office regarding the objectives of the study. After the baseline survey, which will help to identify the indoor smokers, smoking practices, ventilation issues, and waste management practices, a simple randomisation will be undertaken of the selected slums in the urban and peri-urban areas to receive intervention or not.

The allocation sequence generation and the assignment of participants to the intervention will be carried out by the statistician and the investigators will enrol the participants.

*Blinding*: Blinding may not be possible as a lot of people are involved, local self-government officials, the investigators team, health centres, health workers, frontline workers such as the accredited social health activist, and anganwadi workers. The group of people who collect the outcome data will be blinded.

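### The primary outcome names two time points and women and/or children without saying which contrast decides the trial, while the sample size covers one 5% comparison

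*Protocol article*

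**What the plan says.** All references are to the protocol article.

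- **Time.** Under Outcomes, "The primary outcome is SHS exposure at homes at 10 months and 16 months". Both visits are named, neither is ranked, and nothing says whether one or both must succeed.
- **Person.** The same sentence defines the measure as "change in mean urine cotinine levels among women and or children of the smoker at the individual level". Numbers analyzed repeats the wording: "The urine cotinine of the women and children will be obtained from 300 women and or children in each arm". The effectiveness row of Table 2 uses the same and/or formula.
- **Sampling.** The text after Table 1 fixes who gives urine: the smoker's wife or another woman who spends more time in the home, and the youngest child aged over 1 year. It explains that both are needed because "All houses may not have children". Table 1 schedules cotinine for women and for children at all three visits.
- **Analysis.** Outcomes and estimation plans a repeated-measures ANOVA of cotinine and also mixed models testing the change from baseline to each follow-up. Under the correlation aim there is a further comparison, at the final visit with adjustment for baseline. None is named as primary.
- **Sample size.** The calculation is "To detect a minimal difference of 0.03ng/ml in cotinine levels between groups", "at 80% power with a two-sided alfa of 0.05", and "the estimated sample size was 113 indoor smokers per arm for individual randomization". It names no visit and no person.

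**The concern.** A sample size and an error rate describe one decision rule. Here the calculation describes one comparison, while the primary outcome admits several: month 10, month 16, either or both; the woman, the child or a pooled value. Each rule has its own false-positive rate and power, and most do not have the 5% and 80% that are stated.

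If the choice stays open until results are seen, a favourable visit or person could be put forward as the primary result, and a reader could not tell whether it had been chosen in advance. The person matters separately. Homes without a child can contribute only a woman, so an analysis of women, of children and of both together would rest on different numbers of people.

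**Working it through.** **Inputs.** From Sample size calculation: difference 0.03 ng/ml, two-sided alpha 0.05, power 80%, 113 per arm before clustering, ICC 0.06, mean cluster size 20, CV of cluster size 0.45, VIF 2.4, then 271 and finally 300 per arm. From Outcomes: two visits, and women and/or children. No SD and no correlation between tests is given. Both are assumptions below.

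**1. The plan's own figure.**
- VIF = 1 + ((1 + CV²)m − 1) × ICC = 1 + (1.2025 × 20 − 1) × 0.06 = 2.383, stated as 2.4.
- 113 × 2.4 = 271.2, and 271/20 = 13.6, so 14 clusters per arm.
- Dropout of 10%: 271/0.9 gives 302 and 271 × 1.1 gives 299. The stated 300 agrees with either.
- The 113 cannot be checked without an SD. Solving n = 2(1.960 + 0.842)² × (SD/0.03)² for 113 gives an SD of about 0.0805 ng/ml (standardised difference 0.373).

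The chain from 113 to 271 to 300 therefore reproduces as one comparison at two-sided 5%. It contains no allowance for a second.

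**2. Success at either visit, each tested at 5%.** If independent, 1 − 0.95² = 9.75%. By simulation of correlated normal statistics:

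| Correlation (assumed) | At least one false positive |
|---|---|
| 0 | 9.75% |
| 0.5 | 9.1% |
| 0.7 | 8.3% |
| 0.9 | 7.1% |

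False claims of benefit alone are about half of these, against a nominal 2.5%.

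**3. Success at both visits.** There is no alpha inflation. With 80% power at each, joint power is 0.80² = 64% if independent, 69% at correlation 0.5, 71% at 0.7 and 75% at 0.9.

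**4. Ceiling: four separate tests (two visits by two persons), any one sufficient.** If independent, 1 − 0.95⁴ = 18.5%. With both correlations at 0.5, 0.7 and 0.9, the figure is 16.1%, 13.7% and 9.8%.

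**5. Paying for two tests with Bonferroni.** At alpha 0.025 the requirement is 137 × 2.4 = 329 analysed, 329/0.9 = 366 recruited, and 19 clusters per arm. With the planned 271 analysed, power per test is 71%.

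**6. Choice of person.** If children alone decided the trial, with the same SD and ICC and a child in 75%, 50% or 25% of homes (assumed; the share is not given), power would be about 75%, 66% or 48%.

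**7. Woman/child mix.** Suppose women and children differed by one implied SD (0.08) and the child share moved by 10 percentage points in one arm only. A pooled arm mean would shift by 0.10 × 0.08 = 0.008 ng/ml, about a quarter of the 0.03 target. Both figures are assumptions, for illustration.

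All power figures use the normal approximation, without a small-cluster correction.

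**The case against.** Four objections deserve weight.

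- **The persons are defined.** A reader might infer from the and/or wording that nobody in particular is to be measured. That is not so: the text after Table 1 and Table 1 itself say which woman and which child give urine and when. Only whose value is primary remains open.
- **Four tests are not planned.** A reader might infer four chances of success and an 18.5% error rate. The protocol nowhere says that women and children are tested separately or that any one result suffices. The tests also share homes and clusters and would be positively correlated. Four tests is a ceiling. Two is a fair reading, because a test at each follow-up is planned.
- **The mix of women and children is largely set before allocation.** Smokers are recruited and baseline measured before clusters are randomised, the outcome is a change, and baseline and covariate adjustment are planned. A reader might infer that a mixed sample biases the result in itself. It does so only if the mix shifts by arm or visit, for example through differential loss, and a shift shared by both arms would largely cancel from their difference.
- **Multiplicity rules commonly sit in the analysis plan, which is not shown.** Their absence here is no fault. Defining the primary outcome, however, belongs to the protocol, and the definition given has no single value.

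The repeated-measures ANOVA or the final-visit comparison could each supply a single test. But tests at each follow-up stand beside the ANOVA, and the final-visit comparison sits under the correlation aim, so neither settles the question.

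**Conclusion.** The concern holds in this form: the primary outcome does not say which visit, or whose cotinine, decides the trial, and the stated 5% and 80% fit only one comparison chosen in advance.

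The size depends on the rule. If either visit suffices, the family-wise error is about 7% to 9.75%. If both must succeed, alpha is kept and joint power is about 64% to 75%. Four separate tests, at about 10% to 18.5%, is an upper bound that the document neither states nor excludes. These ranges rest on assumed correlations from 0.9 to 0, on 80% power for each test, and on normal approximations. The effect of a changing woman/child mix is conditional on differential loss or missing samples, of which the document gives no evidence.

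**What to change.** State one primary contrast in Outcomes, and repeat it in Sample size calculation and in Outcomes and estimation, before clusters are allocated. Study status reports baseline collection as ongoing, and allocation follows baseline, so there is still time.

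- **Time.** Test the two visits in a fixed, pre-stated order at full alpha: for example month 16, then month 10 only if month 16 is significant. Month 16 is ten months after the month-6 baseline and so is nearer to the one-year horizon of the hypothesis. One pre-stated contrast combining both visits would serve equally well.
- **Person.** Either make the cotinine of the same enrolled woman at every visit primary, with the child's as key secondary. Or keep both in one baseline-adjusted mixed model with a single arm effect, a woman/child term, and household and cluster random effects.

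The choice of person and order is the sponsor's; what matters is that it is written down before the arms exist. The cost is wording. The second visit, and the child result if the woman is chosen, is no longer a stand-alone primary claim. With one contrast, alpha stays at 5% and the stated 300 per arm stands, on the plan's own assumptions.

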### Participants

*Eligibility*: All individuals who have been living in the area for more than 6 months are eligible to participate in the study. In the households the individuals will be screened to identify homes where the male members are between 18-80 years and smoke within the homes. Such male members will be considered for the study and a participation information sheet will be given following which informed written consent will be obtained. In order to determine the impact of passive smoking their spouse or a close female relative will be administered a questionnaire following informed consent. Similarly, children in the house less than 18 years will also be administered the child questionnaire and enrolled in the study after due consent from the legally authorised representative. If there are two children in the study the youngest child older than one years will be enrolled in the study. Single male migrants and household with transgenders will be excluded.

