*Data collection*: Four semi-structured questionnaires have been developed and pretested. They include household, smoker, spouse and child questionnaires. The household questionnaire is for the household and comprises sociodemographic variables, number of family members, identifying the smokers, number of rooms, ventilation, distance from the road, type of road, any other source of air pollution within 500 m, organic and inorganic waste disposal, cooking fuel used, ventilation in the kitchen, use of mosquito coils, incense sticks, and the presence of pet animals. The smokers’ questionnaire will determine smoking habits, age of initiation of smoking, types of tobacco product used, money spent on tobacco per week, quit attempts, frequency and place of smoking within home, smoking when children are around, nicotine dependence score, awareness of harmful effects of second hand smoke, and who influences smokers the most. Nicotine dependence has been assessed by the Fagenstrom scale. The spouse questionnaire will consist of exposure to second hand smoke at home, practice of indoor smoking, ventilation in the kitchen, exposure to second hand smoke outside the home, cleaning habits, cooking practices, and medication use. The child questionnaire will consist of domains on reports of second-hand exposure at home and outside, history of respiratory morbidity in the past 6 months and history of hospital admission. For older children above 12 years the domains will also consist of history of tobacco use, age of initiation, and awareness regarding harm of second hand smoke. Standard methods of measurement of weight and height will be taken of the smoker, spouse and child. Blood pressure of the smoker and spouse will be measured by an electronic sphygmomanometer in a seated position after ensuring that the person is relaxed. If the reading is ≥140/90 mmHg the measurement will be repeated after 30 min and the average of the two will be taken. In order to measure FeV1/FeV6 the smokers will be instructed to take a deep breath and blow hard and long (6 seconds) till a beep is heard. The mouth should be sealed around the disposable mouthpiece. The measurement will be noted down by the health worker. We will also measure SHS through the air pollution monitor within the home which will measure particulate matter of size 2.5 microns and is a marker for the presence of SHS in the home. The device will be charged and left in the home for recording for 6-8 hours at an elevated place. The machine will record PM 2.5, 10 PM. The sensor will record the readings every 5 minutes and the output will be in the form of a graph. After downloading in the evening it will be given in the next house. This will be done at 6, 10, and 16 months respectively (

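### Harm reduction is defined by cigarettes alone while the protocol elsewhere counts cigarettes or bidis; read literally, it misses bidi reduction and credits a switch to bidis

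*Protocol article*

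**What the plan says.** The Outcomes section of the protocol article lists, among the secondary outcomes, "harm reduction (reduction in the number of cigarettes smoked". The matching line of Table 1, under Smoker, is "No of cigarettes smoked daily", ticked at baseline and at both follow-ups. The table has no line for bidis or for total smoked products.

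The population is wider than cigarette smokers. Under Participants, households are screened for homes where "male members are between 18-80 years and smoke within the homes", with no restriction by product. The analysis paragraph adds: "All the smokers will be included in the analysis regardless of reduction in smoking within homes". The smoker questionnaire, described under Data collection, covers "types of tobacco product used".

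The Qualitative data analysis section names bidis twice. The wives' focus groups are drawn partly from households of "those who reduced the number of cigarrettes/bidis", and the end-of-study groups include "those who have reduced the number of cigarettes/bidis smoked and those who did not make any change at all".

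Under Outcomes and estimation, harm reduction is one of the outcomes assigned to a Cox model, so its definition decides who has an event.

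**The concern.** The outcome names one product, the eligibility rule admits smokers of any product, and the qualitative section expects a second product and treats a fall in its use as a reduction. Taken at its word, the definition fails in two ways.

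- A man who smokes only bidis has no cigarettes to reduce. He stays in the denominator and can never be a success.
- A man who replaces cigarettes with bidis is scored as reduced, although he smokes as many sticks as before.

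The first failure costs events and shrinks an absolute difference between arms. The second creates successes that are not reductions; if switching were more common in one arm, it would bias the comparison. At stake is the interpretation of the trial's only quantitative measure of how much enrolled men cut down short of quitting.

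**Working it through.** **No figure of the protocol depends on this definition**, so there is none to reproduce for harm reduction. The check is a comparison of the text, followed by an illustration on assumed inputs.

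**Text, side by side**

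| Place | Unit or scope |
|---|---|
| Outcomes, secondary outcome | cigarettes |
| Table 1, Smoker | cigarettes per day, three surveys |
| Participants, eligibility | any indoor male smoker, 18 to 80 |
| Data analysis and statistical plan | all smokers analysed |
| Data collection | type of tobacco product recorded |
| Qualitative data analysis | cigarettes/bidis (twice), cigarettes alone (once) |
| Outcomes, wives' focus groups | cigarettes alone |

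The outcome definition and its measurement line agree with each other, so the narrow unit is not a single stray word. No sentence states how bidis or dual use enter the count.

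**Literal scoring of individuals**

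- Bidi-only smoker: cigarette count 0 at every survey, change 0 − 0 = 0, whatever happens to his bidi use.
- Switcher from 10 cigarettes to 10 bidis a day: cigarette change (10 − 0)/10 = 100%; change in total sticks 10 − 10 = 0.

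**Literal scoring of the arms.** Let b be the share of smokers who use bidis only. Assume that b is the same in both arms, that the true effect is the same in bidi-only and other smokers, and that bidi-only men are always scored as not reduced. Then

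observed proportion = (1 − b) × true proportion, so observed difference = (1 − b) × true difference.

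A true 20-point difference becomes 20 × 0.8 = 16 points at b = 20% and 20 × 0.5 = 10 points at b = 50%.

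For power, assume true proportions reduced of 20% and 35%. The protocol's sample-size inputs (mean cluster size 20, CV 0.45, ICC 0.06) give a variance inflation of 1 + ((0.45² + 1) × 20 − 1) × 0.06 = 2.383, against 2.4 stated. Dividing its 271 per arm by 2.383 gives an effective 113.7 per arm. A two-proportion power calculation at two-sided 0.05 gives:

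| b (assumed) | Observed proportions | Difference | Power |
|---|---|---|---|
| 0% | 20.0% vs 35.0% | 15.0 points | 72.0% |
| 10% | 18.0% vs 31.5% | 13.5 points | 65.7% |
| 25% | 15.0% vs 26.25% | 11.25 points | 55.5% |
| 50% | 10.0% vs 17.5% | 7.5 points | 37.5% |

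The ratio of proportions does not move: 35/20 = 17.5/10 = 1.75. On a ratio scale, therefore, the bidi-only problem costs mainly events and precision. Switching is different: it adds false events and can distort a ratio as well as a difference.

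The values of b and the proportions 20% and 35% are invented for illustration, and the ICC is borrowed from the cotinine calculation. None of them estimates this trial.

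**The case against.** The strongest reply is that cigarettes is shorthand. The wives' focus groups are described by cigarettes alone under Outcomes and by cigarettes/bidis in the qualitative section. Within the qualitative section, the smokers' groups also carry both labels. The specific aims use a product-neutral term, smoking intensity. What is actually recorded is set by the smoker questionnaire, which the article says is deposited but which is not shown here; it may well count bidis.

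Much of this stands, and it rules out several stronger readings that a reader might infer:

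- *Bidi smokers will in fact be entered as zero and cannot register a change.* This follows only if the label is applied literally. The article does not show the form.
- *The outcome is diluted by a known amount.* The protocol gives no bidi-only share, dual-use share or switching rate.
- *Switching leaves household smoke unchanged.* Only the number of sticks is unchanged; nothing in the article equates the smoke from the two products.
- *The quantitative outcome and the focus groups will classify men differently.* The mixed labels for the same groups do not establish this.

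The shorthand argument does not remove the point. No sentence says that cigarettes include bidis, and elsewhere the article names both when it means both. Nor is this a detail merely left to a fuller document: the article states the unit of the outcome, and states it too narrowly for the men it enrols. If the word is shorthand, the wording needs correcting; if it is literal, the measure does.

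**Conclusion.** The point holds as a conditional one. The stated unit of the harm-reduction outcome does not match the enrolled population or the protocol's own description of reduction in the qualitative section. If the unit is applied literally, bidi-only smokers cannot show a reduction, and a move from cigarettes to bidis counts as one. How much this matters cannot be determined from the article; the illustrative range runs from no loss, if there are no bidi-only smokers, to half of an absolute difference, if half the men smoke only bidis.

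The reach is narrow: one self-reported secondary outcome. A reader might infer that the evidence on second-hand smoke exposure is compromised. It is not: cotinine, PM2.5, reports of smoking inside the home and quitting are not defined by product, and the sample-size calculation is unaffected. The change is still worth making because it is nearly free and the time for it is limited.

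**What to change.** Reconcile the Outcomes section and Table 1 with the qualitative section:

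1. Define harm reduction as a fall in the total number of cigarettes, bidis and any other smoked tobacco products per day, and reword the Table 1 line to match.
2. Count that total in the same way at baseline and at both follow-ups.
3. Report counts by product alongside the total, so that switching is visible.
4. Use the same wording for the focus groups wherever they are described.
5. Confirm that the baseline smoker form captures a bidi count. If it does not, add it now.

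Timing matters. The Study status section says that baseline collection is ongoing, clusters are randomised after it, and the follow-up surveys reuse the same questionnaire. A missing baseline count filled in after allocation would rest on recall by men whose arm may be known to them.

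The cost is two wording edits and, if the form lacks it, one count per product, plus completion of that count in homes already surveyed. A simple total treats products as equal sticks, an equivalence that the article does not support; the product-specific counts make that choice transparent.
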